### Power calculation/sample size

Sample size was calculated taking into account the design effect (due to group randomization) and the expected effect size. The measures with the highest expected effect size within the duration of the study of 20 months are: empowerment (0.38) and hope (0.50) [26, 43]. Cohen’s d was used as the measure for effect size with *α* = 0.05 and a power of 0.80, based on a two-sided test. The design effect used is estimated to be 1.5 based on an average cluster size of 38 and an intra-cluster correlation (ICC) of 0.013. Based on the effect size of empowerment (0.38; the lowest of the two above mentioned) a sample of 128 clients per condition is needed. When taking into account a reduction of 20 % for loss due to follow up, 160 clients per group will be recruited to achieve the required power. To reach a sufficient amount of clients 16 teams will be included in the study, which together provide services to 890 clients.

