### Statistical analysis

Data will be analysed according to intention-to-treat, meaning that participants will be analysed in the group to which they were allocated by randomization [65]. SPSS 19 will be used for the analysis. Because the study has a cluster randomized design, longitudinal multilevel analysis (linear mixed modeling with random intercepts at both team level and individual level) is the analysis method of choice. First, effectiveness of the CARe Methodology on the three primary outcomes, recovery, social functioning and quality of life, will be evaluated. Subsequently, the effectiveness on four secondary outcomes, hope, empowerment, self-efficacy beliefs and need for care will be evaluated. An alpha correction (i.e., Bonferroni adjustment) will be applied across analysis of the primary measures in order to maintain a family-wise alpha level of 0.05. A separate Bonferroni adjustment will be applied to the set of analysis for the secondary measures to maintain their family-wise alpha level at 0.05. Furthermore, in separate analyses we will assess whether different types of predictors explain the outcomes: (1) client characteristics (age, gender, having a partner, type of housing, diagnosis), (2) symptom severity (BSI), (3) health and day care utilization. Only predictors that influence the prediction of the outcome measures will be added tot the final model. Outcomes will be measured at 10 months and 20 months post-baseline (time will be analyzed as a categorical variable).

To detect significant differences in the baseline characteristics between the intervention group and control group descriptive analysis will be used. When necessary these differences will be taken into account in the analysis. Missing data and drop-outs will be analysed and accounted for by multiple imputation if the assumption of data missing at random (MAR) is not violated [66].

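### The family-wise 0.05 is not guaranteed as written, because no single test per outcome is fixed across the two visits; Holm would also be a cheap improvement on Bonferroni

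*Protocol article*

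**What the plan says.** All the relevant text is in the protocol article. Under Statistical analysis, the model is fixed: "longitudinal multilevel analysis (linear mixed modeling with random intercepts at both team level and individual level) is the analysis method of choice". The order of evaluation is given: "First, effectiveness of the CARe Methodology on the three primary outcomes, recovery, social functioning and quality of life, will be evaluated", followed by the four secondary outcomes. The error-rate promise for the primaries is that a "Bonferroni adjustment) will be applied across analysis of the primary measures in order to maintain a family-wise alpha level of 0.05". For the rest, "A separate Bonferroni adjustment will be applied to the set of analysis for the secondary measures to maintain their family-wise alpha level at 0.05". The same section places the outcome visits at 10 and 20 months after baseline and adds that "time will be analyzed as a categorical variable".

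The section does not state a divisor or a per-test alpha. It does not say whether an outcome is judged on one visit, on both jointly, or on either. The Study design section and Table 1 list T1 and T2 side by side without ranking them. The Power calculation/sample size section speaks of effects expected "within the duration of the study of 20 months", but it does so for empowerment and hope, which are secondary outcomes.

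**The concern.** A mixed model with group, categorical time and their interaction has two post-baseline treatment contrasts for each outcome, one at 10 months and one at 20. Three primary outcomes therefore offer six contrasts. The correction is described as running over the measures, and there are three of those. A reader who divides 0.05 by three and then looks at both visits for each outcome would be following the text, and would not be holding the level that the text promises.

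Two analysts could thus apply the same paragraph and work at quite different error rates. The choice of visit or contrast also decides what the primary endpoint is, so it should be settled before outcome data are seen. A second, smaller matter is that the stated procedure gives up some power that a step-down version would keep at the same family-wise level.

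**Working it through.** **Inputs.** From the article: family-wise alpha 0.05 for each of two families; three primary and four secondary outcomes; two post-baseline visits (Statistical analysis); d = 0.38, 128 clients per condition, design effect 1.5, two-sided testing (Power calculation/sample size). Assumed, because the article gives neither: correlation between the T1 and T2 test statistics from 0 to 0.9, and correlation between outcomes from 0 to 0.7.

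**1. The plan's own figure.** With one test per outcome at 0.05/3 = 0.0167, the Bonferroni bound is 3 × 0.0167 = 0.05. Under independence it is 1 − (1 − 0.0167)³ = 0.0492. The stated 0.05 reproduces on this reading.

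**2. Divisor three, either visit counts.** There are six tests at 0.0167.

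- Bound: 6 × 0.0167 = 0.10.
- Independence: 1 − (1 − 0.0167)⁶ = 0.0959.
- Correlated null z statistics, 1,000,000 draws per setting:

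| T1-T2 correlation | between-outcome 0 | 0.3 | 0.5 | 0.7 |
|---|---|---|---|---|
| 0 | 0.096 | 0.093 | 0.087 | 0.076 |
| 0.5 | 0.091 | 0.088 | 0.082 | 0.073 |
| 0.7 | 0.085 | 0.082 | 0.077 | 0.067 |
| 0.9 | 0.071 | 0.069 | 0.064 | 0.057 |

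The range is 0.057 to 0.096, and every setting lies above 0.05.

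**3. Secondary family on the same reading.** There are eight tests at 0.05/4 = 0.0125. The bound is 8 × 0.0125 = 0.10; under independence it is 1 − (1 − 0.0125)⁸ = 0.0957.

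**4. Readings that keep the promise.**

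- One joint 2-df test per outcome at 0.05/3: simulated 0.040 to 0.049.
- One named visit per outcome at 0.05/3: bound 0.05.
- All six contrasts at 0.05/6 = 0.0083: bound 0.05, and 0.0490 under independence.

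**5. Holm against Bonferroni.** Suppose that all three primaries had the article's d = 0.38. The effective number per arm is 128/1.5, so the noncentrality is 0.38 / √(2 × 1.5/128) = 0.38 × √(128/3) = 2.48. Bonferroni power per outcome at two-sided 0.05/3 is 0.535. Holm tests the ordered p-values at 0.05/3, 0.05/2 and 0.05. Its simulated mean power per outcome is 0.619, 0.615, 0.611 and 0.606 for between-outcome correlations of 0, 0.3, 0.5 and 0.7. The gain is about 7 to 8 points. Holm's first step is the Bonferroni test, so the chance of at least one rejection is the same under both; the gain lies in the second and third rejections.

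The same inputs at an unadjusted two-sided 0.05 give power of 0.70 and not the stated 0.80. That is a separate sample-size matter, and nothing above depends on the 0.80.

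**6. Cost of the alternative divisor.** At 0.05/6, power for a single contrast with the same inputs falls to 0.44. Fixing one test per outcome is therefore cheaper than dividing by six.

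**The case against.** The strongest reply is that neither a divisor of three nor separate tests at T1 and T2 is written down. Categorical time is a statement about model coding. A group-by-time term can be tested once per outcome, and the text speaks of effectiveness on three outcomes, which reads as one question for each. Three natural readings hold 0.05 and only one does not. The article is also a condensed account, and the contrast and divisor may be set out in an analysis plan that is not shown.

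Much of this stands. A reader might infer that the family-wise level is breached, but the article does not support that, because it never says that a finding at either visit will count. What remains is that the article does not leave multiplicity for later. It fixes the procedure, both families, the model, the coding of time and the level to be kept, and those choices together do not secure the level. Naming one confirmatory test would.

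A reader might also infer from the 20-month horizon in the sample-size section that T2 is already decisive. That sentence concerns the expected effects on empowerment and hope, and designates nothing for the primaries.

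Finally, Bonferroni is valid and correctly described, so calling it a mistake would be wrong. Holm can be recommended only as a better choice at little cost.

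**Conclusion.** The promised family-wise 0.05 is not guaranteed as written. Whether it would be exceeded depends on a choice that the article leaves open. If 0.05 is divided by three and either visit may support a claim, the family-wise error for the primaries is about 0.06 to 0.10, given the assumed correlations. The bound is 0.10 whatever the correlations, for the primaries and for the secondaries alike. With one joint test or one named visit per outcome, or a divisor of six, the 0.05 is kept.

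The move to Holm is an improvement and not a correction. The rise from about 0.535 to 0.61-0.62 in mean power assumes that all three primaries share the effect size that the article took from empowerment; it gives no effect size for the primaries. If only one primary truly responds, the gain would be small, because Holm relaxes its threshold only after a first rejection.

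**What to change.** Add two sentences to the Statistical analysis section.

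- **One confirmatory test per outcome.** Either name the 20-month between-arm contrast as confirmatory, with the 10-month contrast supportive, or use a joint 2-df test of both visits. Do the same for each secondary outcome.
- **Holm in place of Bonferroni.** Apply Holm's step-down procedure across the three primary tests at family-wise 0.05 and, separately, across the four secondary tests at family-wise 0.05. If Bonferroni is kept, state the divisors as three and four on the basis of one test per outcome.

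No added clients and no change to the design are needed. With the 20-month contrast, 10-month findings are no longer confirmatory. With the joint test both visits stay in the confirmatory question, but a significant result does not say which visit drives it, so the visit-specific estimates should be presented as description. Confidence intervals that match Holm are less simple than Bonferroni intervals.

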## Discussion

This article describes the design of a cluster-randomized controlled trial which aims to investigate the effectiveness of the CARe methodology on (among other things) quality of life, social participation and recovery. This study is the first effect study on the CARe methodology and one of the few studies with a control group on a comprehensive rehabilitation method or strengths based approach [25, 38]. This study is of high relevance because recovery and rehabilitation oriented care has become increasing important for mental health care organizations, especially nowadays as de-institutionalization and participation in society is increasingly being encouraged [14, 43, 67].

The strength of this study is that a broad group of clients with long-term SMI (elderly, double diagnosis, mild intellectual disabilities, inpatient and outpatient) will be included. Most rehabilitation or recovery-oriented interventions are offered only to clients who are motivated to participate in them [35, 55]. Consequently, research on these interventions tends to include only motivated clients. The CARe methodology is for all persons with SMI, and therefore this study includes all clients who choose to participate in the interviews for the study, regardless of their rehabilitation readiness or phase of recovery. The underlying reason for this is that the CARe methodology is a method developed for all kinds of clients, including vulnerable ones. Due to this broad inclusion the participants in this study can be seen as representative of clients with (long-term) SMI. This is not only interesting for the analysis of the effects of the CARe methodology, but it also gives insight into where this group stands in terms of societal participation, recovery, hope, quality of life, and empowerment. Therefore the results of this study will add to our current knowledge.

Another strength of this study is that it includes assessment of the level of implementation of the CARe methodology. In this ‘fidelity audit’ interviews will be conducted with clients, workers, team leaders and CARe coaches on different aspects of CARe methodology. This will make it possible to attribute the outcomes to the level of implementation and/or to specific elements of it. Moreover it will give insight into the most critical elements of the method. This audit is at the same time a limitation because the instrument is not yet fully investigated and validated.

Another limitation of the study is that the effects of the CARe training may be biased because several principles of rehabilitation and recovery are already used in regular practice to some extent, which might bias the ‘care as usual’ condition. However, with the selection procedure designed for the participating teams (pre-selection by the organizations, quick scan) and the fidelity audits in both conditions, we prevent and control for this as much as possible. Also, the fact that professionals as well as clients cannot be blinded for the intervention is a limitation of this study design. It is generally known that it is very difficult to investigate the effectiveness of a complex social intervention in a practical environment in which several influences play a role [68]. Nevertheless, in this study these influences can be taken into account, because they will be measured on individual, organizational and environmental levels. Hence the effects of the CARe methodology can be studied in the complex context of practice.

This study will provide insight into the recovery processes of people with SMI and the effects of a comprehensive rehabilitation method on these processes. The results can be used to improve the CARe methodology and the corresponding training program. Furthermore, the results can contribute to the development of recovery-oriented care in general and the inclusion of people with SMI.
